### Dosage

While administering an anticoagulant drug (nafamostat mesilate: approximately 30-40 mg/hr or heparin approximately 40-60 U/kg one shot + approximately 40-60 U/kg/h), 1 Toraymyxin at a flow rate of 60-120 mL per minute should be administered for 3-6 hours (maximum of 24 hours), and at least 2 doses (maximum 3) should be used. The follow-up will be carried out up to 4 weeks after the end of PMX-DHP. PMX-DHP does not have to be conducted in consecutive days, but the interval between each session must be as short as possible.

The equipment operation for direct hemoperfusion will go as follows (Multimedia Appendix 3):

Prepare the extracorporeal circulation device (blood pump, anticoagulant infusion pump, monitoring of arterial and venous pressure of the inlet and outlet pressure of this product)Precautions before use (inspection of exterior, confirmation of sterilization)Cleaning and primingCirculation:
Insert a double lumen catheter into the patient’s femoral vein or internal jugular vein to serve as the site for blood access

Using a blood pump, perform whole blood hemoperfusion at a flow rate of 60-120 mL per minute, which will be determined according to the patient’s condition

When using this product, anticoagulants (nafamostat mesylate, heparin) are administered by continuous infusion from the blood circuit on the blood removal side.

Duration of extracorporeal circulation is 3 to 24 hours per piece

The maximum working pressure of this product is 66 kPa (500 mHg). Note that the pressure difference between the inlet and outlet of this product may increase due to internal clogging caused by the formation of blood clots.

Heparin or nafamostat will be used in the anticoagulant therapy to be performed for direct hemoperfusion associated with PMX-DHP. Moreover, since the target patients of this treatment are within the scope of heparin and nafamostat, the anticoagulation treatment is not considered as the target treatment of this study.

There are no restrictions on the antiviral treatment for COVID-19; however, in principle, the antiviral treatment will not be changed during the study period.

Concomitant use with cytotoxic or biological treatments (anti-IL-1, anti-IL-6 [tocilizumab or sarilumab], T cell or B cell targeted treatment [rituximab, etc], tyrosine kinase inhibitor or interferon), tumor necrosis factor inhibitor, convalescent plasma, and intravenous immunoglobulin administration for COVID-19 are prohibited. Concomitant use of steroids, including dexamethasone and tocilizumab, is acceptable.

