## Methods

### Study Design

We will conduct a multicenter, prospective, intervention, single-group study to evaluate the efficacy and safety of direct hemoperfusion using PMX-DHP for patients with COVID-19. Efficacy will be evaluated by the primary end point, which is the rate of Ordinal Scale for Clinical Improvement after PMX-DHP of at least 1 point from a status of 4, 5, or 6 on day 15, based on previous studies for COVID-19 treatment (Table 1) [23]. Further, safety will be confirmed by the incidence of serious adverse events and problems. The effect of PMX-DHP will be estimated by setting a control group with background factors from non–PMX-DHP patients enrolled in the COVID-19 registry at participating facilities. Since this study will carry out PMX-DHP, setting up a sham group is difficult in terms of ethics because the therapy is relatively invasive. As such, this study will be carried out as a single-group open-label study and will be compared with a historical control. The historical control will be selected from the COVID-19 registry according to age, gender, and severity of pneumonia.

**Table 1 table1:** Purpose and end points.

Purpose			End points		Validity and reason for selection of end points

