The following exclusion criteria will be used: severe progression of multiple organ failure; P/F ratio of 100 or below; extracorporeal membrane oxygenation (ECMO); hospitalization for more than 15 days; platelet count of 20,000/μL or less; cytotoxic or biological treatments (anti-interleukin [IL]–1, anti-IL-6 [tocilizumab or sarilumab], T cell or B cell targeted treatment [rituximab, etc], tyrosine kinase inhibitor or interferon) within 4 weeks prior to consent; treatment with tumor necrosis factor inhibitor within 2 weeks prior to consent; treatment with convalescent plasma or intravenous immunoglobulin for COVID-19; and consideration by the principal investigator or subinvestigator to be unfit to participate in this study.

In case of nonparticipation in the study, administration of remdesivir, dexamethasone, and tocilizumab will be considered if indicated and not already administered. Furthermore, systemic management including oxygen therapy will be performed for deterioration of respiratory function.

A schematic illustration of the study design is presented in Figure S1 in Multimedia Appendix 1.

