### Statistical Analysis

The main purpose of this study is to verify the efficacy in PMX-DHP cases compared to the control in the COVID-19 registry for the primary end point. Particularly, the efficacy of PMX-DHP will be evaluated by comparing the improvement rate (decrease) of 1 point or more from status 4, 5, or 6 on day 15 based on the eight-category evaluation with the COVID-19 registry.

Not hospitalized with resumption of normal activitiesNot hospitalized but unable to resume normal activitiesHospitalized not requiring supplemental oxygenHospitalized requiring supplemental oxygenHospitalized requiring nasal high-flow oxygen therapy, noninvasive mechanical ventilation, or bothRequiring invasive mechanical ventilationRequiring ECMODeath

The status and the percentage of PMX-DHP cases at each evaluation time will be calculated, and the number and percentage of people whose day 15 status improved by 1 or more points from day 1 will be calculated. Furthermore, the following analysis will be planned for comparison with control cases.

Bias is included when comparing the rate of improvement of control cases for 15 days from the time of hospitalization against cases that underwent PMX-DHP several days after hospitalization. Therefore, the number of days from hospitalization to the date of PMX-DHP administration will be calculated for each case.

The effect of PMX-DHP will be estimated using the propensity score based on the data, which integrates this study and the registry. The propensity score will be created based on age, gender, body temperature, etc, and analysis methods such as matching will be used. A significance level on both sides of 5% will be used.

The following results will be calculated for cases enrolled in this study:

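### Adjacent sentences of the concomitant-treatment rule prohibit and permit tocilizumab, so violation status and the regimen compared with registry controls are not fixed

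*Protocol article*

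**What the plan says.** Four places in the protocol article bear on tocilizumab.

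- **Dosage, last paragraph, first sentence.** The list of prohibited treatments opens "Concomitant use with cytotoxic or biological treatments (anti-IL-1, anti-IL-6 [tocilizumab or sarilumab" and ends "convalescent plasma, and intravenous immunoglobulin administration for COVID-19 are prohibited". Tocilizumab is named as an anti-IL-6 agent.
- **Dosage, last paragraph, second sentence.** "Concomitant use of steroids, including dexamethasone and tocilizumab, is acceptable". Here tocilizumab is allowed, and is grouped with steroids.
- **Eligibility Criteria and Recruitment, exclusions.** Prior use is an exclusion: "anti-IL-6 [tocilizumab or sarilumab], T cell or B cell targeted treatment [rituximab, etc], tyrosine kinase inhibitor or interferon) within 4 weeks prior to consent".
- **Eligibility Criteria and Recruitment, care outside the study.** "In case of nonparticipation in the study, administration of remdesivir, dexamethasone, and tocilizumab will be considered if indicated and not already administered".

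Two further statements define the comparison. Study Design draws the controls from "non–PMX-DHP patients enrolled in the COVID-19 registry at participating facilities" and calls them historical, selected on age, sex and severity of pneumonia. Statistical Analysis says: "The propensity score will be created based on age, gender, body temperature, etc, and analysis methods such as matching will be used".

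**The concern.** The rule on one named drug reverses itself from one sentence to the next. If sites worked from this wording, one site could withhold tocilizumab from a PMX-DHP patient and another could give it, each citing the protocol. A monitor could not classify the use, and an analysis set that depends on protocol violations could not be defined for these patients.

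The efficacy claim rests on a non-randomized comparison of about 30 treated patients with registry controls, so what the treated group may receive is part of the definition of the treatment. If tocilizumab is barred, the question is the effect of PMX-DHP without it. If it is allowed, the question is PMX-DHP on top of care that may include it. The control group has to be built to match whichever is meant. The secondary end points include cytokine changes, and the article itself classes tocilizumab as anti-IL-6, so its use also bears on how those results are read.

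**Working it through.** The article gives no figure on this point, so the check is mainly a comparison of texts.

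**Step 1: apply the rules to specific cases.**

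| Case | Exclusion list | Dosage, sentence 1 | Dosage, sentence 2 | Result |
|---|---|---|---|---|
| Tocilizumab in the 4 weeks before consent | excluded | not relevant | not relevant | clear: ineligible |
| Sarilumab after enrolment | not relevant | prohibited | silent | clear: violation |
| Dexamethasone after enrolment | not relevant | not listed | acceptable | clear: compliant |
| Tocilizumab after enrolment | not relevant | prohibited | acceptable | **contradiction** |

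Only the last case fails, and it fails outright.

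**Step 2: try to read the conflict away.**

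- *Punctuation.* Taken literally, the second sentence treats tocilizumab as a steroid. Taken as steroids such as dexamethasone, and also tocilizumab, it drops that misclassification but still permits the drug.
- *Different periods.* The exclusion covers use "within 4 weeks prior to consent". Both Dosage sentences concern concomitant use, so they cover the same period.
- *An exception to the ban.* The second sentence has no wording of exception, and the first would have no reason to name tocilizumab if it were exempt.

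None of these readings leaves a single rule.

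**Step 3: does the exclusion conflict as well?** No. It is limited to prior use and is clear alone. Excluding recent users while allowing later use would be logically coherent, and so would barring both. The exclusion needs only to be read alongside the reconciled concomitant rule.

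**Step 4: could the comparison shift?** For a simple difference in improvement rates,

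shift = (difference between groups in the proportion given tocilizumab) × (change in the probability of improvement due to tocilizumab).

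The document gives neither input. As a pure assumption, take a difference in use of 0 to 50% and an effect of 0 to 10 percentage points:

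- lower end: 0 × 10 = 0 points;
- upper end: 0.50 × 10 = 5 points, in either direction according to which group uses more.

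For scale, Sample Size Estimation assumes control improvement of 50% to 60% and a ratio of 1.5. The target difference is therefore 0.5 × 50 = 25 points to 0.5 × 60 = 30 points. The assumed upper end of 5 points is 5/30 to 5/25 of it, about one sixth to one fifth. This illustrates scale and does not estimate a bias.

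**The case against.** The strongest case on the other side accepts the contradiction but disputes its consequences.

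- **Eligibility.** A reader might infer that eligibility cannot be applied consistently either. The document does not support this: the exclusion is explicit and time-limited, and nothing in Dosage changes who may enter. This objection stands in full.
- **Controls.** A reader might join the sentence on non-participants to the control pool and conclude that controls received a drug that treated patients were denied. The article describes historical controls from a registry. It nowhere says that non-participants become controls or that registry patients received tocilizumab. This also stands; imbalance is only a possibility.
- **Isolating the effect.** A reader might say that neither reading isolates the effect of PMX-DHP. That goes too far. The Introduction presents PMX-DHP as an addition to usual care, and if tocilizumab is allowed in both groups the comparison is an ordinary add-on one. Residual imbalance is then part of the confounding and selection bias that Limitations partly acknowledges.
- **Analysis detail.** The named propensity-score variables omit concomitant treatment, but the list is open-ended and the analysis plan is not shown. That omission is not a finding.
- **Condensed article.** The full protocol used by sites may be worded differently. That limits what can be said about conduct. It does not excuse the article, because condensation explains missing detail and not two incompatible rules.

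**Conclusion.** The point holds as a direct internal contradiction about concomitant tocilizumab. It rests on the text alone and needs no numerical assumption. Two consequences follow: the violation status of a PMX-DHP patient given tocilizumab after enrolment is undefined, and so is the regimen being compared with registry controls.

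The effect on the primary result is unknown. The 0 to 5 points shown above depend wholly on assumed inputs and are small beside the planned 25 to 30 points, so they do not carry the point. Its weight comes from a treatment rule that cannot be followed or monitored as written, and that costs little to repair. Whether sites actually acted on opposite rules cannot be judged without the full protocol.

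**What to change.** 1. Reconcile the two Dosage sentences into one rule on concomitant tocilizumab, state it consistently with the exclusion for prior use, and remove the grouping with steroids. Which rule is right is a clinical decision for the sponsor.
2. Apply the exclusion's look-back to registry controls, counted back from their index day, and handle use after that day in the same way in both groups.
3. Report tocilizumab use before and after the index day in both groups.
4. Do not rely on an analysis that simply drops patients who received tocilizumab after PMX-DHP started. Such use can reflect deterioration, so dropping these patients conditions on an event after baseline, can itself bias the result, and shrinks a group of about 30.

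The cost is a clarifying amendment with a notice to sites, plus extraction and tabulation of tocilizumab use from the registry; the article does not say whether the registry already holds it. Enrolment was scheduled to end on March 31, 2022. If it has closed, the clarification cannot change conduct. The rule that sites actually followed should then be documented, and the handling of use in both groups fixed, before the comparison with controls is run.

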### Statistical Analysis

The main purpose of this study is to verify the efficacy in PMX-DHP cases compared to the control in the COVID-19 registry for the primary end point. Particularly, the efficacy of PMX-DHP will be evaluated by comparing the improvement rate (decrease) of 1 point or more from status 4, 5, or 6 on day 15 based on the eight-category evaluation with the COVID-19 registry.

Not hospitalized with resumption of normal activitiesNot hospitalized but unable to resume normal activitiesHospitalized not requiring supplemental oxygenHospitalized requiring supplemental oxygenHospitalized requiring nasal high-flow oxygen therapy, noninvasive mechanical ventilation, or bothRequiring invasive mechanical ventilationRequiring ECMODeath

The status and the percentage of PMX-DHP cases at each evaluation time will be calculated, and the number and percentage of people whose day 15 status improved by 1 or more points from day 1 will be calculated. Furthermore, the following analysis will be planned for comparison with control cases.

Bias is included when comparing the rate of improvement of control cases for 15 days from the time of hospitalization against cases that underwent PMX-DHP several days after hospitalization. Therefore, the number of days from hospitalization to the date of PMX-DHP administration will be calculated for each case.

The effect of PMX-DHP will be estimated using the propensity score based on the data, which integrates this study and the registry. The propensity score will be created based on age, gender, body temperature, etc, and analysis methods such as matching will be used. A significance level on both sides of 5% will be used.

The following results will be calculated for cases enrolled in this study:

Pathological improvement rate on day 15 (status 1, 2, and 3 in the eight categories) from the start of PMX. The number and percentage of people who reached status 1, 2, and 3 on day 15 at a 95% CI will be calculated. Furthermore, the same items will be calculated on day 29.P/F improvement on day 4 and 8. The descriptive statistics of P/F on day 1, day 4, and day 8 will be calculated and presented on a transition chart.Changes in cytokines, coagulation markers, and urinary biomarkers. The descriptive statistics of clinical laboratory test values that take continuous values will be calculated. For laboratory findings, which are classification variables, the number and proportions at each level will be calculated at each point in time.Invasive mechanical ventilation avoidance rate and duration of use. The number and proportion of people who underwent invasive mechanical ventilation between day 15 and 29 will be calculated.ECMO avoidance rate and duration of use. The number and proportion of people who underwent ECMO between day 15 and 29 will be calculated.

Similar to the primary end point, the efficacy of PMX will be evaluated for the aforementioned secondary end points using propensity scores based on data integrated with the enrolled cases in the registry.

The safety end point is the incidence and rate of adverse events. Multiplicity will not be adjusted in the analysis of safety end points. In the estimation of the ratio to the number of cases and presence or absence of occurrence, an exact 95% CI for the binomial distribution will be calculated for each group.

In addition to clinical laboratory items, continuous quantity data will be tabulated by group through descriptive statistics, while classification variables will be tabulated through the number of people or rate, among other appropriate methods.

Furthermore, PMX malfunctions will also be tabulated. Subgroup analysis will be performed by status and age at the time of enrollment.

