**Objective:**

This study aims to access treatment options to prevent the transition from acute exacerbation of interstitial pneumonia to DAD. The mechanism of action envisioned for PMX-DHP is to reduce congealing fibrinogenolysis system abnormalities and increase oxygenation by removing activated leukocytes and cytokines, which are risk factors for the aggravation of COVID-19–related pneumonia.

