**Conclusions:**

From a clinical perspective, PMX-DHP is expected to become an adjunctive therapy to address unmet medical needs and prevent the exacerbation from moderate to severe acute respiratory distress syndrome in COVID-19 cases.

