As previously mentioned regarding the clinical significance of PMX-DHP, we believe that COVID-19 aggravates with the rapid deterioration of oxygen saturation, decrease in lymphocytes, and the occurrence of an abnormal congealing fibrinogenolysis system, leading to complex diffuse lung damage. Virus growth suppression caused by antiviral action can be expected if the initial growth rate is suppressed; however, once the condition transitions from moderate to severe, it is most necessary to address unmet medical needs to prevent further exacerbation by providing treatment that will suppress the aforementioned symptoms as soon as possible and prevent the transition to DAD. Simply put, we believe that, in addition to antiviral drugs, it is most necessary to acquire treatment options to prevent progression from rapidly worsening interstitial pneumonia to DAD. The complex mechanism of action envisioned for PMX-DHP is to reduce congealing fibrinogenolysis system abnormalities and increase oxygenation by removing activated leukocytes and cytokines, which are risk factors for the aggravation of COVID-19–related pneumonia. Therefore, from a clinical perspective, PMX-DHP is expected to become an adjunctive therapy to address unmet medical needs and prevent the progression from moderate to severe condition. The scientific rationale of this study is to carry out PMX-DHP, in addition to regular medical care, for patients with COVID-19 and to aggregate and analyze the acquired information. This study will help determine PMX-DHP treatment options in the medical setting by quickly collecting and publishing information on patient background and on the efficacy and safety of treatment by PMX-DHP.

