**Primary**					
	To evaluate the efficacy of PMX-DHP^a^	Improvement rate (decrease) of 1 point or more from status 4, 5, or 6 on day 15 based on the eight-category evaluation		Because it was the primary end point in previous studies for COVID-19 treatment	

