**Secondary**					
	To evaluate the efficacy and safety of PMX-DHP	Pathological improvement rate (status 1, 2, and 3 in the aforementioned eight categories) from the start of PMX^b^. PaO2/FiO2 improvement on day 4 and day 8 Changes in cytokines, coagulation markers, and urinary biomarkers Occurrence of serious adverse events and problems Invasive mechanical ventilation avoidance rate and duration of use ECMO^c^ avoidance rate and duration of use Mortality rate		Evaluation of respiratory function, safety, and efficacy of PMX-DHP	

^a^PMX-DHP: polymyxin B-immobilized fiber column direct hemoperfusion.

^b^PMX: polymyxin B-immobilized fiber column.

^c^ECMO: extracorporeal membrane oxygenation.

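### The stated aim includes preventing progression from moderate to severe disease, but the primary end point counts only improvement and cannot separate stable patients from those who worsen or die

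*Protocol article*

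**What the plan says.** **Aim.** The Objective in the Abstract seeks treatment options to "prevent the transition from acute exacerbation of interstitial pneumonia to DAD". The Introduction states that "PMX-DHP is expected to become an adjunctive therapy to address unmet medical needs and prevent the progression from moderate to severe condition". The Conclusions in the Abstract express the same expectation: to "prevent the exacerbation from moderate to severe acute respiratory distress syndrome in COVID-19 cases". The Objective and the Introduction also name better oxygenation as part of the intended mechanism.

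**Primary end point.** Table 1 defines it as "Improvement rate (decrease) of 1 point or more from status 4, 5, or 6 on day 15 based on the eight-category evaluation". The reason given there is "Because it was the primary end point in previous studies for COVID-19 treatment". Statistical Analysis describes the scoring: "the number and percentage of people whose day 15 status improved by 1 or more points from day 1 will be calculated". On the eight-category scale in that section, 4 is supplemental oxygen, 5 is high-flow oxygen or non-invasive ventilation, 6 is invasive ventilation, 7 is ECMO and 8 is death.

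**Where worsening appears.** Table 1 lists as secondary end points "Invasive mechanical ventilation avoidance rate and duration of use", the equivalent for ECMO, and mortality. Statistical Analysis gives the ventilation count as "The number and proportion of people who underwent invasive mechanical ventilation between day 15 and 29 will be calculated", and uses the same window for ECMO. It also plans subgroup analysis by status at enrolment, and tabulates status at each evaluation time for the PMX-DHP cases.

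**The concern.** An end point should be able to show the effect that the treatment is meant to have. Part of the effect described here is that patients who would have deteriorated do not. A binary outcome of a fall of at least one category places the boundary between improved and unchanged. Everything from unchanged to dead lies on one side of it, so a shift from worse to unchanged leaves no trace.

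Two misreadings are then possible. A null primary result could be taken as evidence against prevention when the end point could not see it. A positive primary result could be taken as evidence of prevention when it shows only that more patients stepped down in respiratory support. Patients at status 6 on day 1 add to this, because for them a move to invasive ventilation has already happened, yet they are pooled in the same rate.

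**Working it through.** **1. The plan's own figures.** Inputs from Sample Size Estimation: 30 treated; 30, 60 or 90 controls; control improvement p0 = 50%, 55% or 60%; p1 = 1.5 × p0; two-sided level 10%. With a continuity-corrected normal approximation,

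power = Φ{[(p1 − p0) − ½(1/n1 + 1/n0) − 1.645 × SE0] / SE1},

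where SE0 uses the pooled proportion and SE1 the separate proportions. For p0 = 0.55 and 30 v 30: SE0 = √(0.6875 × 0.3125 × 2/30) = 0.1197 and SE1 = √(0.825 × 0.175/30 + 0.55 × 0.45/30) = 0.1143. Power = Φ[(0.275 − 0.0333 − 0.1969)/0.1143] = Φ(0.39) = 65%, as stated. The full set is:

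| Control rate | 30 controls | 60 controls | 90 controls |
|---|---|---|---|
| 50% | 53.6% | 66.6% | 72.1% |
| 55% | 65.3% | 78.2% | 83.4% |
| 60% | 78.5% | 89.8% | 93.7% |

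All nine are within 1 point of the stated values. The power figures are not in dispute; they refer to improvement.

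**2. What the score distinguishes.** For a patient at status 4 on day 1, day 15 status 1, 2 or 3 scores as improved. Status 4, 5, 6, 7 or 8 scores as not improved. With 55% of controls improved, the other 45% may all be stable or all be dead, and the primary rate is 55% either way.

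**3. A purely preventive effect.** Let controls be I improved, S unchanged and W worse or dead, with I + S + W = 100%. Suppose PMX acts only on patients who would have worsened, prevents a share k of W, and a share f of those prevented also improve by day 15. Then:

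- primary rate on PMX = I + f × k × W, against I in controls;
- risk ratio for progression = 1 − k.

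Take I = 55% (planning rate, applied here to any mix of statuses) and, as an **assumption**, S = 25%, W = 20%, k = 0.5. The risk ratio for progression is 0.5 in every row:

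| f | PMX improved | Control improved | Ratio (1.5 sought) |
|---|---|---|---|
| 0 | 55% | 55% | 1.00 |
| 0.5 | 60% | 55% | 1.09 |
| 1 | 65% | 55% | 1.18 |

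The first row does not depend on the assumed split: with f = 0 the rates are equal for any W and k. The chance of a significant primary result is then no more than about the nominal level, which is 10% in Sample Size Estimation and 5% in Statistical Analysis (that difference is a separate matter).

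**4. What prevention alone would need.** Reaching 82.5% requires f × k × W = 82.5 − 55 = 27.5 points. W cannot exceed 45%, so f × k must be at least 27.5/45 = 0.61 even if no control patient is stable. For control rates of 50% and 60% the figures are 25/50 = 0.50 and 30/40 = 0.75. With the assumed W = 20%, the most that prevention alone could give is 75%, a ratio of 75/55 = 1.36.

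**5. The opposite extreme.** 82.5% improved and 17.5% dead (about 5 of 30), against 55% improved and 45% stable, would score as the full target effect. This is not a forecast. It shows only that the primary carries no information on the direction taken by non-responders.

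**6. What the other planned outcomes add.**

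- Ventilation and ECMO use are compared with the registry by propensity score, but the window as written omits use that falls wholly before day 15.
- Mortality covers status 8 only.
- The status distribution, which would show worsening directly, is described for PMX-DHP cases and not for controls.
- The subgroups by enrolment status separate patients at 4 and 5 from those at 6, but they do not create a worsening outcome.

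**The case against.** The strongest case on the other side has four parts.

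- **Improvement is a proper efficacy end point.** Table 1 words the primary purpose as evaluating efficacy, and a precedent is cited. The rationale includes better oxygenation, which a step from 6 to 5, 5 to 4 or 4 to 3 reflects. This stands. The point is an incomplete match between aim and end point, not a literal contradiction.
- **Worsening is already covered.** For a patient starting at 4 or 5, ventilation, ECMO and death are statuses 6, 7 and 8; all three are secondary end points, and subgroups by enrolment status are planned. This stands in part. A reader might infer that the plan ignores worsening, which would be wrong. What remains is the day 15 to 29 window and the lack of any scale-based comparison of worsening with the registry. The window may have been meant as by day 15 and by day 29; if so, the wording needs correcting.
- **Equal rates follow from an extreme assumption.** This stands. Some patients kept from worsening would also improve, so 55% v 55% is a limit and not an expected result.
- **The prevention statements are expectations.** The Conclusions say what PMX-DHP is expected to become. They do not say that a positive primary result will be reported as prevention.

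It is also fair to say that the article nowhere equates status 6 with severe disease. Reading a move from 4 or 5 to 6, 7 or 8 as progression is an interpretation, and the Discussion describes the population as moderately to severely ill.

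**Conclusion.** The concern holds in a limited form. The primary end point can support a claim about improvement. It reflects prevention of progression only through the share of prevented progressors who also step down a category by day 15, and it is blind to the rest. Under the assumed 20% progression rate, halved by treatment, the primary ratio lies between 1.00 and 1.18 against the 1.5 sought. The lower limit needs no assumption about the progression rate; the upper one does.

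A reader might go further and infer that the trial would show nothing if PMX works, or that its planned conclusion cannot follow from its results. The documents do not support either. The intended mechanism includes oxygenation, which the primary reflects; the secondary end points capture part of any worsening; and no conclusion from the primary is fixed in advance. The gap concerns which result a prevention claim may rest on, and it can be closed without changing the primary.

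**What to change.** Keep the primary end point and make three changes.

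1. Add a prespecified secondary end point: among patients at status 4 or 5 on day 1, the proportion at status 6, 7 or 8 on day 15, and again on day 29. Compare it with registry controls at status 4 or 5 by the same propensity-score method, and report an estimate with a confidence interval.
2. Count ventilation and ECMO use from day 1, to day 15 and to day 29.
3. State that the primary supports a claim about improvement, and that any claim of preventing progression rests on the progression end point.

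For treated patients the status data are already recorded at each evaluation time, so this is one added analysis; the primary comparison already needs day 15 status from the registry. The day 29 comparison assumes that the registry holds status at that time too.

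The cost is low precision. As a best case, suppose all 30 treated patients start at 4 or 5 and there are 90 controls, with assumed progression of 10% v 20%. The standard error of the difference is √(0.1 × 0.9/30 + 0.2 × 0.8/90) = 0.069, so the 95% interval is about −10 ± 13.5 points, or −23.5 to +3.5, before any effect of matching. The result should be presented as an estimate and not as a test.
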